### Objectives and endpoints

Objectives and endpoints of the TREAT-ME1 study are summarized in Table 1.

**Table 1 Tab1:** **Objectives and endpoints of the TREAT-ME1 study**

Objective	Endpoint
Primary	Safety and tolerability of MSC_apceth_101 (phase I and II)
Key secondary	• Total and individual size of relapse/metastases by CT or MRT according to RECIST criteria (phase I/II, group 1)
	• Detection of the therapeutic transgene expressed by homing MSC in resected tumor specimen by PCR technique shortly after its administration (phase II, group 2)
	• For comparison: Detection of the therapeutic transgene expressed by homing MSC in normal tissue adjacent to the tumor (phase II, group 2)
	• Optionally: PET activity in initially PET positive patients (phase I/II, group 1)
	•Tumor/serum markers (phase I/II, both patient groups)
Other secondary	•Time to progression up to 1 year after first MSC_apceth_101 administration (phase I/II)
	• Overall survival up to 1 year after first MSC_apceth_101 administration (phase I/II)

The Safety Set (SAF) of patients, which will be used for analysis of all safety-related data, will include all patients who received at least one dose of MSC_apceth_101. The Full Analysis Set (FAS) will consist of all patients who received at least one dose of MSC_apceth_101 and have at least one disease assessment. Safety-relevant data to determine the primary endpoint of this trial will include reporting of any adverse event, laboratory and other safety parameters determined in the trial visits.

### Investigation schedule, follow-up and assessments

Tables 2 and 3 illustrate the full investigational schedules for groups 1 and 2, respectively.

**Table 2 Tab2:** **Investigational schedule for patients in group 1 of phase I and II**

Consultation visit	1	2, 6, 10	3, 7, 11	4, 8, 12	5, 9, 13	14	15	16	17	18
Days	(−10) to (−3)	1/8/15	3/10/17	4/11/18	5/12/19	29±3	56±7	168±14	252±14	336±14
**Parameter**	**Screening** ^**1**^	**MSC_apceth_101 infusion** ^**2**^	**GCV infusions** ^**3**^							
**Informed consent**	X									
**Inclusion/exclusion criteria**	X									
**Medical history/demography**	X									
**Physical examination**							X			
**Adverse events**		X	X	X	X	X	X			
**Concomitant medication**	X	X	X	X	X	X	X			
**Vital signs**	X	X^4^	X^5^	X^6^	X	X	X			
**Body weight**	X	X^7^				X	X			
**12-lead ECG**	X					X	X			
**Cardiac monitoring**		X^8^	X^9^	X^10^						
**Oxygen saturation**		X^8^	X^9^	X^10^		X				
**Tumor markers** ^**11**^	X						X			
**Tumor status**	X						X			
**MSC_apceth infusion**		X								
**GCV infusion**			X^12^	X	X					
**MRT or CT (PET optional)**	X^13^						X^14^			
**QoL assessment**	X					X	X			
**Serum pregnancy test**	X						X			
**Urine analysis**	X						X			
**Hematology**	X	X			X	X	X			
**Blood chemistry**	X	X	X	X	X	X	X			
**Creatinine clearance**	X									
**Inflammation markers**	X					X	X			
**Coagulation markers**	X	X			X	X	X			
**Infectious disease markers**	X						X			
**Lymphocyte subsets**	X					X	X			
**Biomarker samples**		X	X	X^10^						
**Retention samples**		X7				X	X			
**Immunogenicity samples**	X					X				
**ECOG**	X						X			
**Disease status** ^**15**^								X	X	X

Footnotes:^1^ not earlier than two weeks after end of chemo-/radiotherapy; ^2^ 24 h (±2 h) inpatient monitoring after end of MSC_apceth_101 infusions;^3^ 24 h (±3 h) inpatient monitoring after start of 1^st^ GCV infusion and including the 3^rd^ GCV infusion (discharge from hospital 2 h after 3^rd^ infusion); ^4^ Before and 15,30,60 min, 2 h, 4 h (±0.5 h), 6 h (±1 h), 8 h (±1 h), 12 h (±3 h), and 24 h (±2 h) after the end of MSC_apceth_101 infusion; ^5^ Before and 15,30,60 min, 2 h, 4 h (±0.5 h), 6 h (±1 h), 8 h (±1 h) after start of 1^st^ GCV infusion and before and 15, 30, 60 min and 2 h after 2^nd^ GCV infusion;^6^ Before and 15, 30, 60 min and 2 h after each GCV infusion; ^7^ Before MSC_apceth_101 infusion; ^8^ Before and 6 h (±1 h) and 24 h (±2 h) after start of infusion of MSC_apceth_101; ^9^ Before and 6 h (±1 h) after start of first infusion of GCV; ^10^ 1.5 h (±0.5 h) after 3^rd^ GCV infusion; ^11^ tumor marker: CEA, CA15-3, CA19-9, CA125, CA72-4, Cyfra21-1, AFP; only tumor marker applying for the tumor entity are determined;^12^ First GCV infusion not earlier than 48 h after preceding MSC_apceth_101 infusion; ^13^ Scans not older than 4 weeks can be used as baseline scans;^14^ MRT or CT or PET whatever was used at visit 1; repeat PET only if PET was done at visit 1; MRT or CT or PET can be carried out up to 28 days after day 56 if this is more convenient for the procedures in the hospital. ^15^ Survival status, any new relapses/metastasis, ECOG, treatment history: chemotherapy, radiotherapy, any other antitumor treatment.

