**Methods/Design:**

TREAT-ME1 is a prospective, uncontrolled, single-arm phase I/II study assessing the safety and efficacy of genetically modified autologous mesenchymal stromal cells (MSC) as delivery vehicles for a cell-based gene therapy for advanced, recurrent or metastatic gastrointestinal or hepatopancreatobiliary adenocarcinoma. Autologous bone marrow will be drawn from each eligible patient after consent for bone marrow donation has been obtained (under a separate EC-approved protocol). In the following ~10 weeks the investigational medicinal product (IMP) is developed for each patient. To this end, the patient’s MSCs are stably transfected with a gamma-retroviral, replication-incompetent and self-inactivating (SIN) vector system containing a therapeutic promoter - gene construct that allows for tumor-specific expression of the therapeutic gene. After release of the IMP the patients are enrolled after given informed consent for participation in the TREAT-ME 1 trial. In the phase I part of the study, the safety of the IMP is tested in six patients by three treatment cycles consisting of re-transfusion of MSCs at different concentrations followed by administration of the prodrug Ganciclovir. In the phase II part of the study, sixteen patients will be enrolled receiving IMP treatment. A subgroup of patients that qualifies for surgery will be treated preoperatively with the IMP to verify homing of the MSCs to tumors as to be confirmed in the surgical specimen.

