### Adverse events (AE)

Registration of any adverse events (AE) following administration of the IMP is a key factor for evaluation of the safety of the IMP. AEs will be defined and evaluated regarding their severity according to the Common Terminology Criteria of Adverse Events (CTC-AE). An AE is defined as the appearance of (or worsening of any pre-existing) undesirable sign(s), symptom(s), or medical condition(s) that occur after a patient received the first dose of IMP and during the following time periods:For phase I and phase II, group 1: from Visit 2 until Visit 15. If any radio- or chemotherapy starts before day 56 the reporting of AEs will be stopped.For phase II, group 2: from Visit 2 until Visit 11 or until start of any radio- or chemotherapy.

It has to be taken into consideration that the safety data evaluation of patient group 2 will be influenced and superimposed by the concomitant surgery and medication and potential other related procedures. The investigator will be asked to evaluate the causal relationship of AE to surgery and/or associated concomitant procedures/medications or to the IMP diligently.

Serious adverse events (SAE) are defined as AEs meeting at least one of the following criteria:Is fatal or life-threateningResults in persistent or significant disability/incapacityConstitutes a congenital anomaly/birth defectIs medically significant, i.e. defined as an event that jeopardizes the patient or may require medical or surgical intervention to prevent one of the outcomes listed aboveRequires inpatient hospitalization or prolongation of existing hospitalization

To ensure patient safety, every SAE regardless of suspected causality, occurring after the patient received the first IMP administration and during the safety time periods as indicated above must be reported in writing within 24 hours of first knowledge of its occurrence. Any SAE arising outside the safety time periods should only be reported if the investigator suspects a causal relationship to the IMP or Ganciclovir.

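### Table 2 schedules no physical examination before dosing in group 1, so signs that only an examination would show have no scheduled baseline for the adverse event definition

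*Protocol article*

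**What the plan says.** The section on the investigation schedule introduces the two tables as complete: "Tables 2 and 3 illustrate the full investigational schedules for groups 1 and 2, respectively".

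In Table 2, which covers phase I and phase II group 1, the row "Physical examination" carries a single mark at visit 15 (day 56±7). The screening cell is empty, and no footnote to the table adds an examination before dosing. In Table 3, which covers phase II group 2, the same row is marked at visit 1 (screening) and at visit 11 (day 29±3).

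The section on adverse events defines one as "the appearance of (or worsening of any pre-existing) undesirable sign(s), symptom(s), or medical condition(s", arising after the first dose of the investigational product. For phase I and phase II group 1 the recording period runs "from Visit 2 until Visit 15". The text below Table 1 ties these records to the main question of the trial: "Safety-relevant data to determine the primary endpoint of this trial will include reporting of any adverse event, laboratory and other safety parameters".

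**The concern.** The definition has two branches, a new sign or a pre-existing sign that has worsened, and both need to know what was present before the first dose. The day 56 examination lies inside the group 1 recording period, so what it finds can become an adverse event. The schedule provides no earlier examination against which to read it.

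The trial is a "prospective, uncontrolled, single-arm phase I/II study", so there is no control group to show how often such signs arise from the disease alone. Each patient's own baseline is the only internal reference. Group 1 patients have advanced, recurrent or metastatic disease for which standard therapy has ended or was not accepted, so signs present before dosing are plausible. A sign first written down on day 56 could then be counted as treatment-emergent when it was not, or put down to the cancer when it was new.

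**Working it through.** No figure in the plan has to be reproduced. The check is a reading of the two tables against the adverse event definition.

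1. **Position of the mark in Table 2.** The header has ten visit columns: screening; the three cycle columns for GCV and the one for cell infusion (four in all); then visits 14, 15, 16, 17 and 18. The examination row has all ten cells, and its only mark is in the seventh, visit 15. Neighbouring rows line up with the header: tumor status, urine analysis and ECOG each show marks in columns 1 and 7. Nothing suggests that the mark moved from another column.

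2. **Comparison with Table 3.**

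| | Examinations before first dose | Examinations after first dose |
|---|---|---|
| Group 1 (Table 2) | 0 | 1 (visit 15, day 56±7) |
| Group 2 (Table 3) | 1 (visit 1) | 1 (visit 11, day 29±3) |

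3. **Comparison within Table 2.** Twenty rows are marked at visit 15. Seventeen are also marked at visit 1: concomitant medication, vital signs, weight, ECG, tumor markers, tumor status, imaging, quality of life, pregnancy test, urine, hematology, chemistry, inflammation markers, coagulation, infectious disease markers, lymphocyte subsets and ECOG. Retention samples have a pre-infusion sample at visit 2. Adverse events start at dosing by definition. That leaves 20 − 17 − 2 = 1 row with no value before dosing: the physical examination.

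4. **What the other screening data cover.** Visit 1 also has "Medical history/demography". Known conditions, and anything visible in vital signs, weight, ECG, blood, urine or imaging, therefore have a baseline. What remains is the set of signs that only an examination would show.

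5. **Patients affected.** All 6 phase I patients follow Table 2, as does the group 1 part of the 16 in phase II. Assuming that each phase II group has at least one patient, the range is 6 + 1 = 7 to 6 + 15 = 21.

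6. **Weight of one error.** If one phase I patient had one sign wrongly classified, the proportion of phase I patients with that event would shift by 1/6, about 17 percentage points. Within one dose of three patients it would shift by 1/3, about 33 points. This illustrates scale only; the documents give no frequency for such signs.

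**The case against.** The strongest reply is that this is a lost mark and not a decision. Nothing in the text says that a screening examination was left out on purpose, the parallel table has one, and the article contains other small slips, such as the safety follow-up section pointing to Tables 1 and 2 for visits that are scheduled in Tables 2 and 3. Eligibility also calls for clinical judgement before dosing, for example on ascites, effusions and heart failure stage. This stands as an explanation. It does not remove the discrepancy: if an examination is intended, Table 2 misstates the schedule, and an examination that is not scheduled need not be recorded in the same way for every patient.

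A reader might infer more than the documents support:

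- **That day 56 findings can never be classed as new or pre-existing.** The screening data in step 4 settle many such questions; only signs specific to an examination are left.
- **That group 1 patients are not examined before dosing.** The blank shows that no examination is scheduled, not that none takes place.
- **That dose escalation or the move to phase II rests on this examination.** The interim analysis is described in terms of adverse events and relevant changes in laboratory values or vital signs, and both of those measurements have a screening value. An examination finding could enter only as an adverse event.
- **That pooled safety data would mix two kinds of baseline.** The article does not state that groups 1 and 2 are pooled, and it warns that surgery will affect the group 2 safety data.

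**Conclusion.** The point holds in a limited form. As printed, Table 2 gives group 1 no scheduled examination before the first dose, in conflict with Table 3 and with an adverse event definition that depends on the state before dosing. The affected data belong to the primary endpoint but form a small part of it: signs that would not appear in the history, vital signs, weight, ECG, laboratory tests, imaging, tumor status or ECOG at screening.

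It concerns all 6 phase I patients and an unstated share of the 16 in phase II. The conclusion rests on the table as printed, on the article's own description of the tables as complete, and on there being no footnote to the contrary. The full protocol is not shown and may already contain the examination. In that case the error is confined to the article's table.

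**What to change.** Reconcile the physical examination row of Table 2 with Table 3 and with the adverse event definition by marking it at visit 1, so that findings on day 56 can be compared with a recorded baseline. If the full protocol already requires a screening examination, correct the published table to say so. How examination findings are then classed as treatment-emergent can be left to the analysis plan.

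The cost is one table entry and a few minutes at a screening visit that already includes vital signs, weight, ECG and ECOG. Sample size, endpoints and analysis are unaffected.

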### Clinical trial population

#### Inclusion criteria

Patients included in this trial, regardless of trial phase, must meet all of the inclusion criteria listed below:Adequate organ function:Hemoglobin > 9.0 g/dlWhite blood cells > 3,000 cells/μl and Neutrophils > 500 cells/μlPlatelets > 100,000 cells/μlSerum ALT/AST ≤ 3 x upper normal limitSerum Total bilirubin ≤ 1.5 upper normal limitSerum creatinine ≤ 2.0 mg/dl and creatinine clearance ≥ 50 ml/minAnticipated minimal life expectancy of at least 6 monthsMen and women of reproductive potential must agree to follow accepted contraception methods during treatment and for 3 months after completion of treatment.Ability of patient to understand character and individual consequences of clinical trialAge ≥ 18 yearsWritten informed consent must be available before any study specific procedure is performed

The following inclusion criteria must be fulfilled for patients in phase I or phase II, group 1:Patients with advanced or recurrent or metastatic GI/HPB adenocarcinoma. Target indications are:adenocarcinoma of the esophagus (cT3NxMx or cT4NxMx),adenocarcinoma of the pancreas (cT3NxMx),adenocarcinoma of the stomach (cT3NxMx or cT4NxMx),intrahepatic cholangiocellular carcinoma (cT3NxMx or cT4NxMx)metastasis from colorectal cancer (cTxNxM1)Premature or scheduled termination of standard therapy (including possible preoperative therapy) due to intolerability/progress/inefficacy or no acceptance by the patient if relapses/metastases are measurable by means of imaging techniques. No relapse or metastases should exceed 5 cm in its maximal diameter.In case of metastases from colorectal cancer:Metastases are unresectableThe total volume of the liver metastases does not exceed 30 % of the total liver volumeIn addition to liver metastases, lung metastases are tolerable, however not more than 10 in number with the largest not exceeding 10 mm in diameterPatients have donated bone marrow for the production of MSC_apceth_101 based on a separate approved protocol. MSC_apceth_101 must have been released for the (autologous) use in the same patient.The presence of progressive disease as clinically assessed by the investigator.

In addition to the before mentioned inclusion criteria, the following inclusion criteria must be fulfilled for patients in phase II, group 2:

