### Exclusion criteria

All patients enrolled in this trial independent of phase/group must not fulfill any of the following criteria:Patients with severe heart disease (NYHA stage III/IV; unstable angina pectoris or myocardial infarction during the last 8 weeks before Visit 1 (baseline)Clinically significant ischemic disease during the last 4 weeks before Visit 1Severe lung disease (COPD GOLD grade III/IV, asthma bronchiale grade IV, lung fibrosis)General condition poorer than ECOG2Clinically proven peritoneal carcinomatosis (e.g. by the presence of ascites)Clinically proven significant pleural/pericardial effusionSerious uncontrolled acute infections less than 3 weeks before Visit 1Patients with HBV/HCV infectionsPatients with HIV infectionImmunodeficiencies or systemic autoimmune diseases (e.g. Crohn’s disease) or known malformations of the gastrointestinal tractActive HSV infections by IgM positivitySecond carcinoma in addition to the underlying carcinoma unless the second carcinoma was curatively and successfully resected more than 5 years before Visit 1 (exception: basal cell carcinoma of the skin, precancerous lesions)Use of any immunomodulatorsNeed for chemotherapy or radiotherapy or cytokine treatment (e.g. interferons, G-CSF or GM-CSF) in the time interval 2 weeks before infusion of MSC_apceth_101 or anticipation of chemo- or radiotherapy during treatment with MSC_apceth_101 and GCV until 2 days after the last administration of GCVKnown addiction to alcohol or drugsPatients requiring corticoids in doses above the Cushing thresholdKnown liver fibrosis or cirrhosisAny concomitant severe disease which could compromise the objectives of this study in the judgment of the investigatorFemale patient who is pregnant or breast feedingParticipation in another clinical trial or observation period, respectively, during the last 4 weeks prior to the first MSC_apceth_101 doseAny surgery in the last four weeks before the administration of MSC_apceth_101History of hypersensitivity to the investigational product or to GCV, Valganciclovir, Aciclovir or ValaciclovirAny contraindication to Ganciclovir according to the product information or the need for drugs interacting with GCV

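### Group 1: a scan up to 4 weeks old may serve as baseline although screening can follow prior therapy by 2 weeks, so the baseline for the RECIST size change can predate the end of that therapy

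*Protocol article*

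**What the plan says.** Table 2 (group 1, phases I and II) places screening, Visit 1, between day −10 and day −3, with the first MSC_apceth_101 infusion on day 1. Footnote 1 sets the earliest screening date relative to prior treatment: "not earlier than two weeks after end of chemo-/radiotherapy". A CT or MRT scan is scheduled at Visit 1, but footnote 13 allows an existing one in its place: "Scans not older than 4 weeks can be used as baseline scans". The footnote gives neither the date from which the 4 weeks are counted nor any condition linking the scan to the end of earlier therapy.

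The only later scan in Table 2 is at day 56 ± 7, and footnote 14 adds that it "can be carried out up to 28 days after day 56".

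Table 1 makes lesion size by RECIST the first key secondary endpoint for group 1, and the study rationale names therapeutic benefit by RECIST as something the trial is meant to assess. The section on general aspects describes the trial as single-arm and uncontrolled.

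The group 1 inclusion criteria accept several reasons for having stopped standard treatment: "Premature or scheduled termination of standard therapy (including possible preoperative therapy) due to intolerability/progress/inefficacy or no acceptance by the patient". They also require this: "The presence of progressive disease as clinically assessed by the investigator".

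**The concern.** A change in lesion size can be attributed to the IMP only as far as the baseline shows the tumour as it was when IMP treatment began. A scan actually made at Visit 1 does this reasonably well: it is at least two weeks after the last chemo-/radiotherapy and a few days before the first infusion. The waiver in footnote 13 loses both properties, because its 4-week allowance is longer than the 2-week interval in footnote 1. An accepted baseline can then show the tumour while the previous therapy was still being given.

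For such a patient the day 56 comparison covers the end of the earlier therapy, the treatment-free interval and the IMP period together. There is no control arm in which the same mixture would occur, and only one scan is scheduled after treatment, so the parts cannot be separated afterwards. Numbers are small (six patients in phase I, and the group 1 share of sixteen in phase II), so a few such patients can colour the description of this endpoint.

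**Working it through.** The plan gives no figure of its own on this point, so there is nothing to reproduce. The check is date arithmetic on the rules in Table 2.

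**Inputs**
- Maximum scan age: 4 weeks = 28 days (footnote 13).
- Minimum interval from end of chemo-/radiotherapy to Visit 1: 2 weeks = 14 days (footnote 1).
- Visit 1: day −10 to day −3; first infusion: day 1 (Table 2). From Visit 1 to the infusion this is 10 to 3 days if there is no day 0, and 11 to 4 days if there is.
- Follow-up scan: nominally day 56, at the latest 28 days later, day 84 (footnote 14).

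**Overlap with prior therapy** = maximum scan age − minimum time from end of therapy to the date from which scan age is counted.

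| 4 weeks counted from | Visit 1 on | Therapy ended at least | Scan can precede end of therapy by |
|---|---|---|---|
| Visit 1 | any day | 14 days earlier | 28 − 14 = 14 days |
| First infusion | day −3 | 14 + 3 = 17 days earlier (18 with a day 0) | 28 − 17 = 11 days (10) |
| First infusion | day −10 | 14 + 10 = 24 days earlier (25 with a day 0) | 28 − 24 = 4 days (3) |

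The overlap is positive under every reading. It is zero for any patient whose therapy ended 28 days or more before the counting date, and for any patient who has the Visit 1 scan.

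**Age of the oldest permitted scan at the first infusion**
- Counted from the infusion: 28 days.
- Counted from Visit 1 on day −10: 28 + 10 = 38 days (39 with a day 0).

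**Share of the measured interval that precedes the IMP** (no day 0). Day 1 to day 56 is 55 days.
- Scan made at Visit 1: 3/(3 + 55) = 5% to 10/(10 + 55) = 15%.
- Scan 28 days before infusion: 28/(28 + 55) = 34%.
- Scan 38 days before infusion: 38/(38 + 55) = 41%.

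If the follow-up scan moves to day 84 (83 days after day 1), the last two become 28/111 = 25% and 38/121 = 31%.

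**Does another rule close the gap?**
- The exclusion of chemo-/radiotherapy "in the time interval 2 weeks before infusion of MSC_apceth_101" is tied to the infusion and says nothing about the scan. It is also weaker than footnote 1, which already implies at least 17 days.
- Required progression is a clinical judgement, and no post-therapy image is demanded for it.
- The reasons for stopping therapy include scheduled end, intolerability and refusal, so entry is not confined to patients with a fresh scan showing failure.

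None of these dates the baseline scan relative to the end of therapy.

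**The case against.** The strongest reply is that the exposure is narrow and the consequence modest. Overlap needs both a recent end of therapy and use of an older scan, and the article does not show how many patients that would be. The primary endpoint is safety. The step from phase I to phase II rests on safety data, and the article states no test or decision rule on lesion size. All of this stands, and it limits the weight of the point.

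It can also be said that a condensed article may have dropped a qualifier that the full protocol contains. That is possible for the counting date. But the article does state a rule, and the rule as stated, read with footnote 1, admits on-therapy scans.

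Several stronger readings are tempting and are not supported:
- **That shrinkage from earlier therapy will be credited to the IMP.** Entry requires progression, so a patient still responding to earlier therapy would not normally qualify. Because the judgement is clinical, the case is not excluded, but it is the less likely direction.
- **That a definite amount of tumour growth, or a definite share of a progression threshold, falls before treatment.** The article gives no growth rate and does not restate a threshold, so any such figure would rest on outside assumptions. Part of any such growth would also remain under an ordinary 28-day window.
- **That all tumour-response information is compromised.** Table 1 also lists optional PET activity and tumour/serum markers as key secondary endpoints, and footnote 13 is not attached to the markers.
- **That the entry limits on lesion size are checked on the old scan.** The criterion "No relapse or metastases should exceed 5 cm in its maximal diameter" names no scan, and Table 2 schedules the eligibility check and tumour status at Visit 1.
- **That time to progression is measured against the old scan.** Table 1 gives its time frame from the first administration and does not state the imaging reference.

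**Conclusion.** The concern holds in a limited form. As written, footnotes 1 and 13 of Table 2 together permit a group 1 baseline scan made up to 14 days before the previous chemo-/radiotherapy ended (counting from Visit 1), or about 3 to 11 days before (counting from the first infusion). The missing counting date leaves the maximum age of the scan at the first infusion anywhere from 28 to about 38 days.

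For the patients concerned, the RECIST size change from baseline to day 56 includes time before the IMP, about 34% to 41% of the interval in the extreme cases with a scan on day 56. The likelier bias is pre-treatment growth counted against the IMP; residual benefit of earlier therapy counted in its favour is possible but less likely. The primary safety endpoint is unaffected.

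The figures rest only on the intervals in Table 2. They are maxima, not expected values, and the number of patients affected is unknown. This is a worthwhile, inexpensive correction to a key secondary endpoint and not a threat to the trial's main conclusion.

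**What to change.** Reword footnote 13 so that an existing scan may serve as baseline only if it was made after the end of the previous anti-tumour therapy and no more than 28 days before the first MSC_apceth_101 infusion. Otherwise, the Visit 1 scan already scheduled in Table 2 is the baseline.

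This brings the overlap to zero under either reading, fixes the counting date and caps the age of the scan at 28 days instead of about 38. It does not remove pre-treatment growth within those 28 days, so the scan date and the date of the last prior therapy should be listed for each patient beside the size change.

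The cost is one footnote. Some patients with a recent on-therapy scan lose the waiver and need the Visit 1 scan. No visit is added.
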